### Sample size

Study sample size calculation was conducted in G* Power (version 3.1). Based on previous study findings
^
36
^, 15 participants per group are required to detect a mean difference of 3.7 seconds in time to complete TUG with 80% power and significance at p<0.05. Additionally, based on the same findings
^
36
^, 16 participants per group will be needed to detect a mean difference of 1.52 in MNA-FF score between the intervention group and the control group with 80% power and significance at p<0.05. To ensure an adequate sample size to enable per protocol analysis, the sample size was increased to 23 participants per group
^
46
^. This will allow for both intention-to-treat and per-protocol analyses, ensuring rigorous analysis of intervention effectiveness.

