### Statistical analysis plan

Statistical analyses will be performed using SPSS Statistics for Windows, version 27 (SPSS Inc., Chicago, Ill., USA) and RStudio (2023.06.2. Posit, PBC) as appropriate. Data cleaning will be conducted prior to analysis.

Demographic data and study primary and secondary outcomes will be described using measures such as mean and standard deviation, median and interquartile range, 95% confidence interval, or count and percentage. Descriptive statistics will also be used to report the feasibility of the intervention. Missing data will not be imputed for the primary analysis.

Data will be analysed using the intention-to-treat approach, wherein all participants who have been randomly allocated to the study intervention
^
80
^ will be included. The between-group and within-group difference at baseline (T1), post-intervention (T2) and 12-weeks post-intervention (T3) in primary and secondary outcomes will be analysed using either parametric or non-parametric, based on the normality of data distribution. The primary outcome is TUG and MNA-FF post-intervention (T2). Further, a mixed between-within linear model will be used to assess group, time, and group x time interaction effects. Between-group linear mixed-model analysis will be used to assess the mean difference in change from baseline to post-intervention. The dependent variables will be TUG and MNA-FF with group (ONS + RT, RT), time (baseline, post-intervention), and the group-by-time interaction as fixed factors; participant ID as a random factor; and baseline values as covariates. Effect sizes (partial eta squared) will be calculated using the Cohen’s d classification (0.01 = small, 0.06 = moderate, 0.14 = large). Variables not normally distributed will be transformed as appropriate. The proportion of participants whose TUG and/or MNA-FF improved or deteriorated post-intervention (T2) will be calculated. The interindividual variability in response to the ONS will be calculated using the Atkinson and Batterham formula
^
81
^.

Using the same approach as above, between-group differences and within-group differences at baseline (T1), post-intervention (T2), and 12 weeks post-intervention (T3) will be analysed for secondary outcomes.

A per-protocol analysis will also be conducted, including participants who adhered to the intervention and have baseline (T1) and post-intervention (T2) measurements
^
82
^.

A p-value of less than 0.05 will be considered statistically significant.

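### The only fully specified model for TUG and MNA-FF uses the T1 value both as a response and as a covariate, so its effect estimate is not baseline-adjusted and its standard error may be modestly too small

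*Protocol article*

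**What the plan says.** The article's section Statistical analysis plan fixes the time point of interest: "The primary outcome is TUG and MNA-FF post-intervention (T2"). It then lists several analyses: parametric or non-parametric comparisons between and within groups at each visit, a mixed between-within model, and finally one model set out term by term. The purpose of that last model is given as follows: "Between-group linear mixed-model analysis will be used to assess the mean difference in change from baseline to post-intervention". TUG and MNA-FF are its dependent variables, and its terms are group, "time (baseline, post-intervention), and the group-by-time interaction as fixed factors; participant ID as a random factor; and baseline values as covariates".

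The section does not call this model the primary analysis, but no other model for the two primary outcomes is fully specified. It gives no estimation method, residual covariance structure or degrees of freedom. The secondary outcomes are to be analysed in the same way, so the specification may carry over to them.

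**The concern.** Two standard models have been merged. One takes T1 and T2 as responses and reads the treatment effect from group-by-time. The other takes T2 as the response and adjusts for T1. Each is valid alone. In the merged form the T1 value is on both sides of the equation.

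Two things are at stake. First, a reader who sees a baseline covariate will take the reported effect to be baseline-adjusted. With 23 participants per arm, chance imbalance at T1 is likely, so the distinction matters. Second, a covariate that equals one of the two responses distorts the variance components on which the standard error rests.

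**Working it through.** **Inputs from the article.** Model terms as above; 1:1 allocation; "the sample size was increased to 23 participants per group"; significance level 0.05 (sidedness not stated, two-sided assumed). The sample sizes of 15 and 16 per group come without an SD, so they cannot be reproduced forwards. Solved backwards with a two-sided t-test at 80% power, they imply standardised effects of about 1.06 and 1.02. Only the 23 is used below, and the point does not affect the sample size.

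**Assumptions.** The article gives no T1–T2 correlation rho; the 0.99 quoted for TUG is rater reliability. I take rho from 0.3 to 0.9, complete pairs, normal data, and SD 1 at both times unless stated.

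**Step 1: the estimate.** Write Y_it = a + b·g_i + c·t + θ·g_i·t + γ·Y_i0 + u_i + e_it. Subtracting a participant's two rows gives Y_i1 − Y_i0 = c + θ·g_i + (e_i1 − e_i0). Both γ·Y_i0 and u_i drop out, so the estimate of θ is the difference in mean change. In one simulated data set it was 0.308 with the covariate, without it, and from a change-score test; ANCOVA on the same data gave −0.305. The correlation of the θ estimate with chance baseline imbalance was −0.51 at rho 0.5 and −0.32 at rho 0.8, against about 0 for ANCOVA.

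**Step 2: efficiency.** The variance of a change score is 2(1−rho) and the ANCOVA residual variance is 1−rho². Their ratio is (1−rho²)/[2(1−rho)] = (1+rho)/2, which is 0.75 at rho 0.5. For a true effect of 0.845 SD with 23 per arm and rho 0.5, power is 80% for the change score and about 90% for ANCOVA.

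**Step 3: the standard error.**
- Between participants: given Y_i0 and group, the participant mean has residual variance (1−rho²)/4. With two rows each, E(MSB) = (1−rho²)/2.
- Within participants: E(MSW) = 2(1−rho)/2 = 1−rho.
- E(MSB)/E(MSW) = (1+rho)/2, which is below 1. A random intercept needs MSB above MSW, so a variance bounded at zero is set to zero.
- The fit is then ordinary least squares on 92 rows with 92 − 5 = 87 df, and its residual variance is close to (MSB+MSW)/2. Model SE / true SE ≈ sqrt[(3+rho)/4].

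At rho 0.5, MSB = 0.375, MSW = 0.5 and the pooled value is 0.4375. Model SE = sqrt(0.4375 × 4/23) = 0.276; true SE = sqrt(0.5 × 4/23) = 0.295; ratio 0.935.

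Simulation under no effect (20,000 trials per rho for type I error, 23 per arm):

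| rho | Variance at zero | SE ratio, formula | SE ratio, simulated | Type I error | ANCOVA / change variance |
|---|---|---|---|---|---|
| 0.3 | 100% | 0.908 | 0.90 | 7.6% | 0.65 |
| 0.5 | 99.5% | 0.935 | 0.93 | 6.9% | 0.75 |
| 0.7 | 95.5% | 0.962 | 0.96 | 6.1% | 0.85 |
| 0.8 | 88% | 0.975 | 0.97 | 5.8% | 0.90 |
| 0.9 | 70% | 0.987 | 0.98 | 5.5% | 0.95 |

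Repeat runs agreed within about 0.2 percentage points on type I error. Part of the inflation comes from the 87 df: with 44 df throughout, the range is 7.3% to 5.3%.

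**Step 4: unequal SDs.** With s = SD at T2 / SD at T1, E(MSW) − E(MSB) = (1 − rho·s)²/2 in units of the T1 variance. This is never negative, and it vanishes as rho·s approaches 1. At s = 0.8 (rho 0.5 and 0.7) type I error was 8.3% and 7.9%. At s = 1.2 (rho 0.5 and 0.8) it was 6.2% and 5.5%.

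**Step 5: baseline used once.** ANCOVA at T2 gave type I error of 4.9–5.1% and a calibrated SE at equal SDs. The change-score model without the covariate was also valid (4.8–5.1%).

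**The case against.** The strongest reply is that the article does not fix enough to produce the inflation. It names a participant random factor but no estimation method, and a condensed article may leave that to a separate plan. An unstructured covariance, or testing group-by-time against the within-participant mean square, gives a valid test. The mean-square version is the change-score t-test with 44 df, with simulated type I error of 4.9–5.1% at every rho. The section also reports partial eta squared, a sum-of-squares measure, so such an analysis is not far-fetched. This stands: the standard-error problem is conditional on a bounded variance.

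Three further limits stand:
- **Not labelled primary.** A reader might infer that the designated primary test is invalid. The text never gives this model that status, and the other listed comparisons do not have the defect.
- **Not biased.** A reader might infer a biased treatment effect. Under randomisation the difference in change is unbiased, and change is the stated target. The ANCOVA gain is one of efficiency.
- **Exact cancellation needs complete pairs.** With 10 of 46 participants lacking T2 at rho 0.5, the zero-variance fit gave 0.050 against 0.074 for the completers' change difference in one data set, and −0.223 against −0.288 in another.

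None of this removes the contradiction. The specification puts T1 on both sides, and nothing else in the article corrects it.

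**Conclusion.** The model is wrong as written, and the consequence is modest. With complete pairs, its group-by-time estimate receives no baseline adjustment, whatever rho is. The precision forgone relative to ANCOVA is a variance factor of (1+rho)/2 at equal SDs, with rho assumed.

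The standard error is too small only if the random-intercept variance is constrained to be non-negative, as standard REML software does. The shortfall is then about 2–10% at equal SDs, with type I error about 5.5% (rho 0.9) to 7.6% (rho 0.3). It is too small for the change-score estimate it accompanies, not for ANCOVA: at rho 0.5 the mean model SE is 0.275 and the ANCOVA SE 0.257. The documents do not support an unconditional statement that the standard error is wrong. This should be fixed, but it does not undermine the trial.

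**What to change.** Use baseline once, and state which form applies:
- **Baseline as covariate.** Take T2 as the response, or T2 and T3, with the T1 value as covariate; add baseline-by-time if T3 is included.
- **Baseline as response.** Keep T1 as a response, constrain its mean to be equal in the two arms, use an unstructured covariance, and drop the baseline covariate. This form also keeps participants who have only T1, which suits the stated intention-to-treat rule.

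In either case, report the group difference at T2 with its 95% CI for TUG and for MNA-FF, and say whether the same form applies to the secondary outcomes.

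The cost is one sentence in the analysis section, with the same data and software. The choice should be made before results by arm are seen, because the two readings can give different estimates, as Step 1 shows.

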### Qualitative data analysis plan

The free text comments of the acceptability questionnaires will be used to further explore the acceptability of the ONS and online RT intervention and relevant barriers and facilitators to the intervention. Braun and Clarke’s framework of thematic analysis will be used to identify themes and subthemes. This includes familiarisation with the data, creating initial codes, searching for themes, reviewing potential themes and, finally, defining themes and subthemes.

### Dissemination of findings

The study results will be disseminated through peer-reviewed journal article(s) and presented at relevant scientific conferences. The study will be disseminated to healthcare professionals such as community nurses, dietitians, gerontologists and physiotherapists as well as to volunteer organisations for older adults. The results of the study will be reported to the funder (Nutricia Ireland Ltd).

## Discussion

Interventions to improve the physical function and nutritional status of older adults with sarcopenia risk are needed
^
5,
83
^. The POWER Study aims to evaluate the combined effects of a novel whey protein ONS combined with an online RT programme compared to the RT programme alone on TUG and MNA-FF in community-dwelling older adults at risk of sarcopenia who receive supportive home care.

ONS are commonly prescribed in clinical settings to improve dietary energy and/or protein intake in those unable to take adequate nutrition through food sources alone
^
84
^. The ONS provided in this study contains whey protein, shown to stimulate muscle protein synthesis in older adults
^
85
^. It is also enriched with the essential amino acid leucine and vitamin D, both of which have been previously shown to have additional benefits on muscle strength, mass and physical function in older adults
^
34,
85
^. Two servings per day will enable participants to comply with European Society for Clinical Nutrition and Metabolism guidelines for ONS (600 kcal and 40 g protein daily)
^
84
^.

RT is a safe strategy to increase muscle mass, strength and physical function in older adults with sarcopenia
^
86
^. Providing RT online can make exercise more accessible to those who lack transport and, if supervised, can improve adherence since participants are monitored
^
87
^. A recent systematic review and meta-analysis concluded that RT combined with whey protein supplementation in older adults with sarcopenia improved grip strength, increased energy and protein intake and reduced inflammatory markers compared to placebo
^
88
^. Moreover, whey protein supplementation had a significant effect on gait speed, ADL scores, and blood biomarkers, including albumin, Insulin-like Growth Factor-1 and 25-hydroxyvitamin D
^
88
^. However, given that the studies conducted to date varied in type and intensity of RT, protein supplement quantity and intervention duration, the authors advised that more studies should be conducted to validate their review findings and further explore the effects of whey protein and RT in patients with sarcopenia
^
88
^. Furthermore, older adults receiving supportive home care are an often-overlooked cohort in multicomponent interventions who deserve consideration
^
89
^.

This online RT programme, developed with a registered physiotherapist and exercise physiologist, follows the American College of Sports Medicine guidelines
^
90
^ and sarcopenia RT prescription recommendations
^
18
^. This intervention will provide a structured, supervised exercise programme, encouraging participants to stay committed, which will aid adherence
^
44
^. Exercises will be appropriately modified and monitored throughout the intervention. As with other programmes delivered via an online platform, a limitation to this study will be that some older adults will not have access to Zoom (via laptop or tablet), therefore limiting their ability to participate. However, it provides a viable alternative for those unable to access a centre or facility for in-person RT programmes
^
91
^.

Assessments 12 weeks post-intervention (T3) will examine the long-term effects once the intervention ceases. Although participants may show good adherence to the online RT programme, they may discontinue RT once the programme stops
^
92
^. Therefore, the sustained effects of the interventions on physical function, nutritional status and health-related outcomes will be examined 12 weeks post-intervention.

A limitation of this study includes lack of a placebo supplement; therefore, intervention blinding will not be possible. A specific stipulation by the UCD Ethics Committee, given the vulnerability of the study population, was that dietary advice should be provided to all participants to promote an increase of dietary protein through food sources. Providing dietary advice to all participants may act as a confounding factor, making it challenging to isolate the effects of the ONS from changes due to the dietary advice. In addition, as both groups are undertaking the online RT programme, following a similar design to previous research in a vulnerable population
^
36
^, the effectiveness of the RT programme alone compared to no exercise is not possible to determine. However, in addition to the primary analysis comparing the outcomes between ONS + RT versus RT alone, the statistical approach will allow for main effects of time to be identified across both groups, which can be interpreted in relation to minimal clinically important differences. Furthermore, collecting biomarkers of muscle protein synthesis or 25-hydroxyvitamin D (25(OH)D) level will not be possible. Older adults who are housebound in Ireland are recommended a daily supplement of 20 µg of vitamin D, due to limited sun exposure and insufficient intake through food
^
33
^. Hence, participants currently taking vitamin D supplements will not be excluded from the current study.

## Conclusion

In summary, the POWER Study will provide data on the effectiveness and feasibility of an ONS combined with a 12-week online RT programme compared to the RT programme alone, in older adults with sarcopenia risk who receive supportive home care. It will also provide information on whether any changes observed following the intervention are maintained, 12 weeks post intervention. This will contribute to knowledge of how these interventions affect physical function and nutritional status and inform future research and practice.

## Ethics

### Declaration of Helsinki

The study will be conducted in compliance with the Helsinki declaration
^
93
^.

## Approvals

Ethics and consent to participate: The study was submitted for ethical approval to the UCD Human Research Ethics Committee (HREC) on 24 October 2022. Following review and addressing queries, the study was approved (LS-22-59-[name]) on 31 January 2023. The POWER study was registered on ClinicalTrials.gov (NCT05688956) in December 2022. To broaden recruitment within the Irish Health Service Executive (HSE), the study was submitted to and approved by the Clinical Research Ethics Committee Galway (C.A 3058; 6 July 2023) for Community Healthcare Organisation (CHO) area 2 (Co. Galway, Co. Roscommon and Co. Mayo, Ireland) and by the HSE Research Ethics Committee Midlands Area and Corporate (Co. Wicklow, Dun Laoghaire, Dublin South East, Co. Laois, Co. Offaly, Co. Longford, Co. Westmeath, Co. Louth and Co. Meath, Ireland) (RRECB1023CC; on 17 January 2024). Adverse events will be recorded and reported to the UCD and relevant ethics committees.

Written informed consent will be obtained at the baseline assessment in the participant’s home prior to any study related procedures being undertaken. The consent form is available at the UCD Research Data Zenodo Community repository (Appendix C)
^
45
^.

### Declaration of Generative AI and AI-assisted technologies in the writing process

The authors declare that they have not used Generative AI and AI-assisted technologies in the writing process.

## Data Availability

No data are associated with this article. Zenodo: Protein Supplement and Exercise Training for the Treatment of Sarcopenia Risk in Older Adults (POWER),
https://doi.org/10.5281/zenodo.14856935
^
45
^. This project contains the following extended data: SPIRIT checklist Nutritional content of the ONS Participant consent form Study design and participant flow figure Data are available under the terms of the
Creative Commons Attribution 4.0 International license (CC-BY 4.0). UCD Research Data Zenodo Community: This protocol study will be reported following the Standard Protocol Items: Recommendations for Interventional Trials (SPIRIT) with a summary checklist reported (Appendix A) for ‘Oral nutritional supplement combined with an online resistance training programme to improve physical function and nutritional status in older adults receiving home care and at risk of sarcopenia: protocol for the randomised controlled POWER trial’
https://doi.org/10.5281/zenodo.14856935
^
45
^. Data are available under the terms of the
Creative Commons Attribution 4.0 International license (CC-BY 4.0).
